**Materials and methods::**

Prospective, single-center, randomized, double-blind study in esophagectomized patients, and treated after surgery with parenteral lipid emulsions of ω-3 fatty acids or a mixture of ω-6 long-chain triglycerides/short-chain triglycerides 50%. These emulsions will be added to the standard nutritional support in continuous infusion until 5 days of treatment have been completed. Patients will be randomized 1:1:1 in Group A receiving 0.4 g/kg/d of fish-oil lipid emulsion and 0.4 g/kg/d of a lipid emulsion mixture of ω-6 long-chain fatty acids (LCT) plus medium-chain fatty acids (MCT) (total dose of 0.8 g/kg/d of lipid emulsion); Group B receiving 0.8 g/kg/d of fish oil lipid emulsion and Group C receiving 0.8 g/kg/d of LCT/MCT emulsion.

The main objective is to determine whether 5 days administration of intravenous ω-3 fatty acid lipid emulsion is effective in normalizing interleukin-6 levels compared with LCT/MCT emulsions, and whether a 0.8 g/kg/d dose is more effective than 0.4 g/kg/d. Secondary outcomes include other inflammatory markers such as C-reactive protein, tumor necrosis factor alpha and interleukin-10, and parameters of morbidity, safety, nutrition and mortality.

Samples will be collected at the time when surgery is indicated and on days 0, 1, 3, 5 and 21 to determine inflammatory, nutritional, hepatic and safety parameters. In addition, clinical follow-up will be continued throughout the hospital admision and up to 1 year after surgery.

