### Study objectives

2.1

The main objective of this study is:

To establish if the endovenous administration of ω-3 fatty-acid fish-oil lipid emulsions for 5 days in esophagectomized patients is effective in reducing inflammation – measured as seric concentration of interleukin-6 (IL-6) – compared to the administration of lipid emulsions of LCT/MCT. Additionally, to determine if doses of 0.8 g/kg/d are more effective than doses of 0.4 g/kg/d in the normalization of IL-6.

The secondary objectives aim to determine if the intravenous administration of ω-3 fatty-acid fish-oil lipid emulsions for 5 days in esophagectomized patients shows differences compared with the administration of LCT/MCT lipid emulsion with regard to:

Seric concentration of other inflammatory parameters: C-reactive protein, tumoral necrosis factor-α (TNF-α), interleukin-10 (IL-10), interleukin-8 (IL-8) and soluble interleukin-2 receptor. In addition, in the follow-up, whether these markers, alone or in combination, show equal or greater efficacy of effect on the inflammatory response compared to IL-6.Post-operative complications: suture dehiscence, chylotorax, pneumonia and other infections.Safety, measured as hepatic impairment and alterations in coagulation parameters.Nutritional parameters: albumin, prealbumin and lymphocytes.Mortality: evaluated at hospital admission and at 1 year post-surgical intervention.

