#### Number of participants subjects and trial duration:

2.2.3

Recruitment will last a total of 24 months from the approval date. Each subject will participate in the trial for a year post-surgical intervention.

On the basis of the results obtained and as referenced by Furukawa et al^[19]^ (a study of the values of IL6 in esophagectomized patients who received parenteral nutrition with ω-6 fatty acids or without lipids), and considering that the effect of administration of fish-oil emulsion (with ω-3 fatty acids) will be similar to the non-administration of ω-6 fatty acids, a sample size of 33 patients is estimated for 80% of potency and 5% of alfa error with 10% of anticipated losses.

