### Study variables

2.3

The main variable of this study is the variation of seric concentration levels of IL6 at randomization and on days 1, 3, 5, 21 post-surgery in esophagectomized patients receiving fish-oil lipid emulsions parenterally for 5 days compared with those receiving LCT/MCT emulsions.

The secondary variables will examine whether intravenous administration of fish-oil lipid emulsions instead of LCT/MCT for 5 days leads to differences from randomization and on days 1, 3, 5 and 21 post-randomization with respect to:

Seric concentrations of inflammatory markers: RCP, TNF-α, IL-10, IL-8 and soluble interleukin-2 receptor.Morbidity measured as post-operative complications: suture dehiscence, chylotorax, pneumonia and other infections.Safety measured as hepatic impairment (total bilirubin, alanin-aminotranspherase, aspartate-amino transpherase, gammaglutamil transpherase, alkaline phosphatase) and alteration in coagulation parameters (INR, prothrombin time, platelet count).Nutritional parameters: albumin, prealbumin and lymphocytes.Mortality measured for a year after surgical intervention.

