##### Analytical data

2.5.1.1

-Inflammatory parameters: values of IL-6, RCP, TNF-α, IL-10, IL-8 y CD25 on days 0, 1, 3, 5 and 21 post-surgery will be recorded. These values have been selected according to what is reported in the literature in similar studies.^[19–25]^ Also, these same values will be recorded pre-operatively at the time surgical intervention is indicated to show the patient's baseline inflammatory status.-Nutritional parameters: albumin, prealbumin and lymphocytes at the time surgical intervention is indicated and on days 0, 1, 3, 5 and 21.-Hepatic parameters: total bilirubin, alanin-aminotranspherase, aspartat aminotranspherase, gammaglutamil transpherase and alkaline phosphatase at the time surgical intervention is indicated and on days 0, 1, 3, 5 and 21.-Safety: INR, prothrombin time and platelet count at the time surgical intervention is indicated and on days 0, 1, 3, 5 and 21.

The total number of blood extractions per patient will be 6.

Clinical data: the following data will be recorded:

-Post-surgery complications such as chylothorax, dehiscence, pneumonia and other infections.-Mortality: from the day of surgery to 1 year following surgery.-Nutritional support: the amount of EN received by each patient will be recorded to determinate total calories administered.

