#### Statistical analysis

2.6.1

Descriptive statistics will be employed for all collected variables data, such as baseline values for inflammatory, nutritional, hepatic and safety parameters, in frequency tables. For continuous variables, statistical descriptions will be used (n, average, standard deviation, value range and median), meanwhile grouped percentages will be used for categorical variables.

The main objective is to establish the difference between basal values of inflammatory parameters and values at day 5 post-randomization, and to assess differences between days 1, 3 and 21. The secondary objectives are to establish the difference between basal values of morbidity, safety and nutritional parameters and those values at day 5 post-randomization.

Significance will be calculated using Student's *t* test for matching data or Wilcoxon-test (non-parametric test) depending on whether normality can be assumed or not. To establish the differences among the 3 groups for the same period of time, Student's *t* test (parametric test) or Mann Whitney *U* test (non-parametric test) will be used, depending on whether normality can be assumed or not. For categorical variables, the chi-square test or the Fisher test will be used when necessary.

The significance level will be established with a 95% confidence interval (CI). Data will be processed with SPPS v 19.

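### The baseline-to-day-5 analysis stated for morbidity does not fit post-operative complications, and it conflicts with the objective, time points and follow-up given elsewhere in the article

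*Protocol article*

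**What the plan says.** The statistical section (2.6.1) sets the secondary analysis in one sentence: "The secondary objectives are to establish the difference between basal values of morbidity, safety and nutritional parameters and those values at day 5 post-randomization". The sentence before it, on inflammatory parameters, also names day 5 but adds days 1, 3 and 21. No further days are added for morbidity.

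Other parts of the article treat the same endpoint differently:

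- Section 2.1 asks whether fish oil "shows differences compared with the administration of LCT/MCT lipid emulsion with regard to" a list that includes post-operative complications. This is a question between arms.
- Section 2.3 gives the definition, "Morbidity measured as post-operative complications: suture dehiscence, chylotorax, pneumonia and other infections", and asks whether treatment "leads to differences from randomization and on days 1, 3, 5 and 21 post-randomization with respect to" that item and the other secondary variables.
- Section 2.5.1.1 lists "Post-surgery complications such as chylothorax, dehiscence, pneumonia and other infections" among the clinical data to record, with no time limit.
- The abstract says that "clinical follow-up will be continued throughout the hospital admision and up to 1 year after surgery", and section 2.2.3 that "Each subject will participate in the trial for a year post-surgical intervention".

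Section 2.6.1 also provides for comparisons among the three groups over the same period, and names the chi-square or Fisher test for categorical variables. It gives no event definition or window for these tests.

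**The concern.** A change from baseline makes sense for albumin or bilirubin, which are measured before surgery and again on day 5. It does not suit an event that can only follow the operation. The sentence puts both kinds of variable under one rule, and the rule fits only the laboratory values.

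Two things are at stake. First, followed as written, complication counting stops on day 5. Section 2.2 gives the lipid infusion for 5 days after surgery, so counting would end about when treatment ends, and later leaks and infections would fall outside the stated analysis. Second, the article supports at least three windows: day 5, day 21, and the hospital admission or longer. If none is fixed beforehand, the choice could be made after the results are known. In arms this small, one or two events can change how the result reads.

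**Working it through.** The article states no figure for morbidity, so there is none to reproduce. The check is mainly a comparison of its sections.

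**1. Is there a basal value?** Section 2.5.1.1 schedules pre-operative sampling for inflammatory, nutritional, hepatic and coagulation parameters, and none for complications. No complication score is defined from which a change could be taken. Every patient is free of post-operative complications before surgery, so

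change to day 5 = (status at day 5) − 0 = occurrence by day 5.

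The contrast can be read in this way, but only as a short-window incidence. A paired pre/post test would then show only whether complications occurred at all, not whether the arms differ.

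**2. Do the sections agree?**

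| Feature | Section 2.6.1, secondary-objectives sentence | Elsewhere in the article |
|---|---|---|
| Contrast | Basal value against day 5 | Fish oil against LCT/MCT (2.1) |
| Time points | Day 5 only | Days 1, 3, 5 and 21 (2.3); no limit on recording (2.5.1.1); through the admission and clinical follow-up to 1 year (abstract) |
| Time origin | Randomization | Randomization for secondary variables, surgery for IL-6 (2.3); surgery for the inflammatory samples (2.5.1.1) |

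The time origin matters because the article does not state the interval between randomization and surgery. If randomization came *k* days before surgery, day 5 post-randomization would be post-operative day 5 − *k*, which is before the infusion ends. The value of *k* is unknown; with *k* = 0 the two clocks agree.

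**3. What can this sample show?** Section 2.2.3 gives 33 patients, set for IL-6, and section 2.2.2 allocates them 1:1:1: 33 / 3 = 11 per arm. Suppose one arm has no event and another has *x* events. The two-sided Fisher p-value with 11 per arm is 2 × C(11, *x*) / C(22, *x*):

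- *x* = 4: 2 × 330 / 7315 = 0.090
- *x* = 5: 2 × 462 / 26334 = 0.035

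So even against an arm with no events, 5 of 11 patients with a complication are needed to reach 5%.

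For power, complication rates must be assumed, because the article gives none. Take a risk of 30% to 60% in one arm, halved in the other, and a two-sided 5% normal approximation with pooled variance under the null:

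power = Φ{ [p1 − p2 − 1.96 √(2 p̄(1 − p̄)/n)] / √[(p1(1 − p1) + p2(1 − p2))/n] }

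- n = 11, 30% against 15%: Φ[(0.15 − 1.96 × 0.178) / 0.175] = Φ(−1.14) = 13%
- n = 11, 60% against 30%: Φ[(0.30 − 1.96 × 0.212) / 0.202] = Φ(−0.57) = 28%
- n = 10 per arm (33 × 0.90 = 29.7 patients after the 10% losses, about 30): 12% and 26%

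These figures count every complication. A shorter window captures no more events.

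**The case against.** The strongest defence is that section 2.6.1 must be read whole. Complications are categorical, a chi-square or Fisher test is named for categorical variables, and comparisons among the three groups are foreseen. A valid between-arm test is therefore already available. Section 2.3 carries morbidity to day 21. A condensed article may also leave exact event windows to the full protocol or the SAP.

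Much of this stands. It would be wrong to say that no between-arm test is planned, or that the article as a whole stops at day 5. But the named test comes with no window, and the only time point that the statistical section gives for morbidity is day 5 against baseline. This is not missing detail: the article states a contrast that does not suit the endpoint and that disagrees with its own sections 2.1 and 2.3.

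A reader might go further in three ways that the documents do not support.

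- *Deaths after day 5 are lost.* The sentence does not mention mortality. Section 2.5.1.1 records "Mortality: from the day of surgery to 1 year following surgery", and sections 2.1 and 2.3 also carry it to 1 year. Its absence from one summary sentence imposes no day-5 rule.
- *A known share of complications is discarded.* The article gives neither complication rates nor their timing, so any such percentage would only restate an assumption.
- *Complications are already recorded for every patient to 1 year.* Section 2.5.1.1 gives them no window; only mortality has an explicit 1-year limit. Section 2.2.1.1 excludes patients with grade IV surgical complications, or with treatment-related adverse effects, from the study, so their later data may not exist.

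**Conclusion.** The point holds for complications. The analysis stated for morbidity is wrongly specified: taken literally it has no baseline, and read generously it is incidence by day 5, about the end of the infusion. It conflicts with the between-arm objective in 2.1, with the days listed in 2.3, and with follow-up through the admission in the abstract. The time origin is also inconsistent.

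The number of complications left out cannot be derived from the documents. The finding rests on the wording of the sections and on the fact that post-operative events cannot precede surgery; it needs no assumed rate. Power is low whichever window is used (13% to 28% for a halved risk at 11 per arm, under the assumed rates), so the correction gives an interpretable, pre-specified secondary endpoint and not a powered one. It should be made, but it does not affect the IL-6 analysis.

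**What to change.** 1. In section 2.6.1, remove morbidity from the baseline-to-day-5 sentence and keep that sentence for the laboratory safety and nutritional parameters.
2. Add, for example: *For each type of complication, and for any complication, the number and proportion of randomised patients with at least one event from surgery to [day 21 or discharge, one to be chosen] will be compared between arms with the chi-square or Fisher test, with risk differences and 95% confidence intervals.* The horizon should lie within the follow-up already stated and be fixed before unblinding.
3. Reconcile sections 2.1, 2.3, 2.5.1.1 and 2.6.1 on contrast, window and time origin (surgery or randomization).
4. State how patients excluded under section 2.2.1.1 enter the count, since the denominator is all randomised patients.
5. Describe the comparison as descriptive or low-powered.

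The cost is a change of wording, using tests already planned. Before choosing the horizon, the sponsor should confirm that complications are recorded to that point for all patients, including those excluded; if they are not, the data collection instructions also need a line.

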#### Patients recruitment, randomization and allocation

2.2.2

All patients allocated for EPG following medical criteria, and those who meet the inclusion criteria will be candidates to participate in the trial.

The surgical team will be responsible for communicating the possibility of participating in this trial when IC is obtained for the surgical intervention. IC for participation in this trial will be collected before randomization.

Subjects will be randomized to 3 groups (1:1:1) by a pharmaceutical researcher after recruitment by the surgical team:

Group A will receive 0.4 g/kg/d of fish-oil LE and 0.4 g/kg/d of a LE mixture LCT/MCT receiving a total dose of 0.8 g/kg/d of LE over 5 days post-surgery,Group B will receive 0.8 g/kg/d of fish-oil LE,And Group C will receive 0.8 g/kg/d of a LE mixture of LCT/MCT 50%.

This allocation will be blind for all patients and health personnel. The allocation sequence (computer-generated random numbers) will be generated by the pharmaceutical researcher and it will be performed by randomized blocks permutated with the block size defined at random. In the first step, blocks of size 3 with possible sequences ABC, ACB, CAB and CBA, and size 6 will be defined. In a second step the clusters will be randomized, and in a third step the sequences will be randomized within the blocks. This method ensures that the groups are balanced throughout the study, and that the researcher cannot predict the sequence. The pharmaceutical researcher will be responsible for patient assignation to the corresponding intervention group, and will also assign a numbered patient identification code for each patient in the trial. The composition of the emulsion administered to each patient will only be known by: the pharmaceutical researcher responsible for clinical trials, the pharmaceutical researcher who will validate its conduct, and the personnel who will conduct it.

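### Two-group tests at an undivided 5% level for a three-arm, two-question primary objective leave the family-wise error on IL-6 at about 9–12% at day 5 alone

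*Protocol article*

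**What the plan says.** All references are to the protocol article.

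- **Arms (2.2.2):** "Subjects will be randomized to 3 groups (1:1:1) by a pharmaceutical researcher after recruitment by the surgical team".
- **Main objective (2.1):** it holds two questions. The first is whether fish oil "is effective in reducing inflammation – measured as seric concentration of interleukin-6 (IL-6) – compared to the administration of lipid emulsions of LCT/MCT". The second is "to determine if doses of 0.8 g/kg/d are more effective than doses of 0.4 g/kg/d in the normalization of IL-6".
- **Main variable (2.3):** "variation of seric concentration levels of IL6 at randomization and on days 1, 3, 5, 21 post-surgery". No day is set above the others here.
- **Analysis (2.6.1):** the main objective is restated as the change from baseline to day 5, with days 1, 3 and 21 also assessed, and for inflammatory parameters in the plural. Then, "To establish the differences among the 3 groups for the same period of time", the article names Student's t or Mann-Whitney U according to normality. It sets one significance level, matching a 95% confidence interval. No overall three-group test is named.
- **Sample size (2.2.3):** "a sample size of 33 patients is estimated for 80% of potency and 5% of alfa error with 10% of anticipated losses". The 5% is not divided.

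**The concern.** Student's t and Mann-Whitney U each compare two groups. Applied to three arms, they become up to three tests (A–B, A–C, B–C), each at 5%. The primary objective needs at least two of these contrasts, one for each question, and the main variable is measured on four post-surgery days. Followed as written, the rules allow a primary IL-6 claim from any of several tests, while the trial is described and sized as if one 5% error applied. At stake is how far a reader can trust a positive statement about fish oil, or about the higher dose, from a trial of 33 patients.

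**Working it through.** **Inputs from the article:** three arms at 1:1:1, N = 33, alpha 5%, power 80%, losses 10%, two primary questions, four post-surgery days.

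**Assumptions:** two-sided tests (sidedness is not stated), normal data with equal variances, no true difference between arms, equal correlation between days. The correlation is not given, so a range is shown.

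**Step 1. The plan's own figure.** N = 33 cannot be rebuilt, because the article gives neither a difference nor an SD for IL-6. It can be worked backwards: 33 × 0.9 = 29.7, or about 10 evaluable patients per arm (equivalently 30 × 1.10 = 33). With 10 per arm and an undivided 5%, 80% power needs a standardized difference of (1.960 + 0.842) × √(2/10) = 1.25 SD by the normal formula, or 1.32 SD by the noncentral t. So 33 corresponds to a single two-group comparison with alpha undivided and an effect of about that size.

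**Step 2. Upper reference for the family-wise error.** For k independent tests at 5%, the error is 1 − 0.95^k:

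- k = 2: 1 − 0.9025 = 9.75%
- k = 3: 1 − 0.8574 = 14.3%
- k = 12 (three pairs × four days): 1 − 0.5404 = 46.0%

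**Step 3. Allowing for dependence.** Contrasts that share an arm are correlated. For B–C and B–A the covariance is σ²/n and each variance is 2σ²/n, so the correlation is 0.5. Days within a patient are correlated too. Simulating 60,000 trials under the global null, with 10 per arm and pooled two-sample t tests at two-sided 5%, gives the chance of at least one false positive:

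| Family of IL-6 tests | Day 5 only | Four days, correlation 0.3 | Four days, 0.5 | Four days, 0.7 |
|---|---|---|---|---|
| One contrast | 5% | 18% | 16% | 13% |
| Two contrasts sharing an arm | 9% | 30% | 27% | 23% |
| All three pairs | 12% | 39% | 35% | 30% |

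At the extremes of 0.9 and 0, the three-pair, four-day figure runs from 22% to 41%. The within-arm paired tests in 2.6.1 are not counted.

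**Step 4. Does a gate restore 5%?** With three arms, if any two of the pairwise null hypotheses are true, all three are. The closed family is therefore the overall null plus the three pairwise nulls. Testing the overall null at 5%, then each pair at 5% only if the overall test rejects, controls the family-wise error. Simulation of an F test followed by pairwise tests at one day gave 4.9% and, in a repeat, 5.1%: 5% within simulation error.

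**Step 5. Price of splitting alpha instead.** At the 1.32 SD effect with 10 per arm, Bonferroni for two contrasts (0.05/2 = 0.025) lowers power from 80% to about 70%. For three contrasts (0.05/3 = 0.0167) it falls to about 63%. Restoring 80% would take 13 or 14 evaluable patients per arm, or 44 or 47 in total after 10% losses (39/0.9 and 42/0.9, rounded up). A gate or a fixed order avoids dividing alpha.

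**The case against.** The strongest reply has three parts.

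First, section 2.6.1 puts baseline to day 5 first, and that day matches the five days of treatment, so day 5 can fairly be read as primary. This has force: the 30–39% needs the less favourable reading, in which the days listed in 2.3 all count. It does not remove the point, because 9–12% remains at day 5 alone.

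Second, testing order, adjustment and the exact contrasts are commonly left to an analysis plan, which is not shown and may settle them. Their absence is therefore not the point here. What can be judged is what the article does state: two-group tests for a three-group question, at one undivided level. An analysis plan could place a gate or an order around those tests, but nothing in the stated rule does so.

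Third, the article never promises family-wise control, and each single test keeps its nominal 5%. That is correct, and the point concerns only the primary IL-6 family.

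A reader might infer more than this, on two counts. The plural wording in 2.6.1 could suggest that all six inflammatory markers are primary, which would give a far larger error rate. Sections 2.1 and 2.3 do not support that: they make IL-6 the main variable and list the other markers as secondary. A reader might also infer that contrasts would be picked once results are known. Nothing in the article suggests it, and the trial is described as double-blind.

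**Conclusion.** The point holds as a matter of family-wise error on the primary IL-6 claim. Followed as written, the rules give about 9% (two contrasts) to 12% (three pairs) at day 5, not 5%. They give about 30–39% for three pairs if all four days are primary. The day-5 figures rest on 10 evaluable patients per arm, two-sided tests and normal data. The four-day figures rest also on an assumed between-day correlation of 0.7 to 0.3. This should be fixed, but it does not undermine the design: IL-6 is already ranked above the other markers, day 5 is already given some priority, and the remedy is wording.

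**What to change.** 1. In 2.3 and 2.6.1, name IL-6 change from baseline to day 5 as the single primary variable. State whether day 5 counts from surgery or from randomization, since the two sections differ.
2. Replace the stand-alone pairwise tests with an overall three-group test at two-sided 5%: one-way ANOVA F, or Kruskal-Wallis if normality cannot be assumed. Follow it with pairwise contrasts at 5% only if it is significant. Alternatively, fix in advance an order of contrasts that covers both primary questions and stops at the first non-significant one. Either route is sufficient.
3. Report days 1, 3 and 21, and the other inflammatory markers, as secondary, with confidence intervals and no confirmatory claim.

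The change is to statistical wording, best made before unblinding, and needs no extra patients. It costs some nominally significant results and some power for the gated contrasts. If a fixed order puts the dose question last, its power cannot exceed the chance that every earlier step succeeds, so the order should be chosen with that in view.

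### The primary IL-6 comparison has no fixed test or scale: an unspecified normality judgement on about 10 patients per arm decides, and one prespecified log-scale analysis adjusted for baseline would be better at almost no cost

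*Protocol article*

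**What the plan says.** Section 2.6.1 (Statistical analysis) states the target this way: "The main objective is to establish the difference between basal values of inflammatory parameters and values at day 5 post-randomization". Section 2.3 describes the outcome differently: "The main variable of this study is the variation of seric concentration levels of IL6 at randomization and on days 1, 3, 5, 21 post-surgery". Neither section says whether IL-6 is analysed raw or transformed, or whether groups are compared on change or on the level at each day.

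For comparing groups, section 2.6.1 offers Student's t or Mann-Whitney, and one of them "will be used, depending on whether normality can be assumed or not". The within-group comparison has the same switch between the paired t-test and the Wilcoxon test. No normality criterion is given.

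On size, section 2.2.3 says "a sample size of 33 patients is estimated for 80% of potency and 5% of alfa error with 10% of anticipated losses". Section 2.2.2 splits these patients equally over three arms.

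Section 2.5.1.1 lists a pre-operative sample, taken when surgery is indicated, and a day-0 sample. Which of them is the basal value in section 2.6.1 is not stated.

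**The concern.** A rule that picks the test after looking at the data leaves the estimand open. The t-test addresses a difference in means, and Mann-Whitney addresses a shift in ranks. The rule covers six inflammatory markers, several days and three pairs of arms, so results could be reported on a mixture of the two.

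At about 10 patients per arm, a normality check is also a weak guide. If IL-6 is right-skewed, the check will often pass and a t-test will be run on skewed values.

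The scale matters more than the choice between tests. If raw change from baseline is analysed, all the baseline variation enters the outcome. Depending on how high baseline is, that could take the primary comparison far below the stated 80% power.

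**Working it through.** **1. Evaluable patients.** Section 2.2.3 gives 33 patients and "10% of anticipated losses". 33 × 0.9 = 29.7, and 29.7 / 3 = 9.9, so about 10 per arm.

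**2. The plan's own figure.** N = 33 cannot be reproduced forward, because no effect size or SD is given. The only basis is an earlier study and the premise "considering that the effect of administration of fish-oil emulsion (with ω-3 fatty acids) will be similar to the non-administration of ω-6 fatty acids". Working backwards with "5% of alfa error" (two-sided assumed), 80% power and 10 per arm, the detectable pairwise standardised difference is (1.96 + 0.84) × √(2/10) = 1.25, or about 1.33 with the noncentral t. The loss allowance fits: 30 × 1.1 = 33.

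**3. Day-5 values only.** Assumptions, none of them in the documents: log-normal IL-6, 10 per arm, and an effect set so that a log-scale t-test has 80% power. The check-then-test rule uses Shapiro-Wilk at 5% in each arm.

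| log SD | both arms pass the check | check-then-test | raw t-test always |
|---|---|---|---|
| 0.3 | 77% | 80% | 79% |
| 0.5 | 58% | 78% | 74% |
| 0.7 | 37% | 78% | 68% |
| 1.0 | 16% | 77% | 57% |
| 1.3 | 6% | 75% | 43% |

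The log t-test gives 79-81% throughout. The check often misses the skewness, yet the rule loses only about 1 to 5 points and its type I error stays at 4.7-5.5%, because the rank test takes over when skewness is marked. The loss grows if normality is accepted too readily: with a lax Kolmogorov-Smirnov check, which passes in 86-100% of trials, power is 74, 69, 61 and 53% at log SD 0.5, 0.7, 1.0 and 1.3.

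**4. Change from baseline to day 5.** Let log baseline and log day-5 IL-6 have the same SD (about 0.6 to 1.0) and correlation ρ (about 0.3 to 0.5). Let treatment lower day 5, and let *k* be the ratio of baseline to control day 5. The effect is set so that log day 5 adjusted for log baseline has about 78% power.

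| Baseline relative to control day 5 | Check-then-test on raw change | t-test on log change | Log day 5 adjusted for log baseline |
|---|---|---|---|
| well below (*k* = 0.14 to 0.37) | 59-76% | 60-70% | 76-80% |
| equal (*k* = 1) | 30-47% | 60-70% | 76-80% |
| 2.7 times higher | about 12% | 60-70% | 76-80% |

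A second calibration, with the effect set for 80% power on the log-scale t-test and log SD 0.5 to 1.0, shows the same pattern. Raw change has 72-92% power with baseline well below day 5, 39-58% with baseline equal, 14-17% at 2.7 times and 6-7% at 7.4 times.

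**5. Where the loss comes from.** On raw change, check-then-test and Mann-Whitney throughout agree to within about 3 points (39% against 40% at log SD 0.8, ρ 0.5, equal baseline). So the check is not the cause; raw subtraction is. With equal log SDs, the raw variance of baseline is *k*² times that of control day 5. At *k* = 2.72 this is 2.72² = 7.4, which swamps an effect that sits only on day 5. At *k* = 0.37 it is 0.14, and subtraction adds little noise.

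**6. Why log change alone is not enough.** Log change has variance 2σ²(1 − ρ), while the adjusted analysis has σ²(1 − ρ²). The ratio is 2/(1 + ρ): 1.54 at ρ = 0.3 and 1.33 at ρ = 0.5. That is why log change reaches only 60-70%.

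**7. Does the choice of test change conclusions?** In simulations of raw change (log SD 0.6 to 1.0, ρ 0.3 to 0.5), the t-test and Mann-Whitney disagreed on significance in 5-22% of trials. In those trials the unstated normality judgement decides the result.

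**The case against.** The strongest reply has three parts.

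First, the between-group sentence in section 2.6.1 concerns groups at the same time point. Read that way, day-5 levels are compared, the rank test deals with skewness, and almost nothing is lost. This stands for power, and it is why the choice step cannot be called costly. It does not settle the reading, because the same section states the main objective as a difference between basal and day-5 values, and section 2.3 speaks of variation in IL-6.

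Second, this is a condensed article. Transformation and normality criterion are commonly left to a fuller document, and nothing here excludes a log scale. That stands as far as silence goes. But the article does more than stay silent: it states a data-dependent rule for the primary test, and that rule can be improved as written.

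Third, the skewness of IL-6 is assumed, and the size of any loss turns on the baseline level, which the documents do not give. This also stands. With baseline well below day 5, raw change usually equals or beats log change, and part of its remaining gap to the adjusted analysis reflects baseline adjustment, not scale.

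**Conclusion.** The point holds as a cheap improvement. Section 2.6.1 fixes neither the test nor the scale for the primary comparison and lets an unspecified judgement on about 10 patients per arm decide, so the quantity tested can vary across markers, days and arms.

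A reader might infer that choosing the test after a normality check forfeits a large part of the 80% power. The figures do not support that: with a Shapiro-Wilk check the choice costs about 1 to 5 points on day-5 values and essentially nothing on raw change.

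A reader might also infer that the trial will fall well short of 80%. That is not established. It needs three things together: raw change as the outcome, right-skewed IL-6, and a baseline as high as or higher than day 5. Power is then about 30-47% (equal) or about 12% (2.7 times higher), against 76-80%. With a pre-operative or other baseline well below day 5, little is lost to the raw scale. The documents give no IL-6 values and do not say which sample is basal, and the stated 80% cannot itself be verified. All power figures rest on log-normal IL-6 and the assumed SDs, correlations and baseline ratios.

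**What to change.** In section 2.6.1, replace the normality-dependent choice with one prespecified analysis for all between-group cytokine comparisons. Model log IL-6 at day 5 on treatment group and log baseline IL-6, and state whether baseline is the pre-operative or the day-0 sample. Report ratios of geometric means with 95% CI. Let no normality test decide the method, and keep the rank test as a named sensitivity analysis. Treat the other cytokines in the same way. Do not substitute log change alone, since it is not reliably better than raw change.

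The cost is a few sentences of analysis text, with no extra patients or samples. The downside is that effects are reported as ratios, not as differences in pg/ml.
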